## Methods

### Study Design

#### Intervention/clinical trial

The primary objective of this study is to explore the feasibility of a GQ intervention in patients with various cancer types who experience CRF. This study includes the 3 most prevalent cancer types that is, breast, lung and colon cancers. This is a randomized-controlled trial that compares the GQ intervention group to a usual care waitlist control group receiving standard medical care allocated in a 1:1 ratio to evaluate the feasibility and effects of a 12-week GQ intervention on 60 eligible breast, lung, and colorectal cancer survivors’ fatigue, sleep quality, depression, and 24-hour urine cortisol change. Refer to Figure 1 for an overview of the study. This study protocol was developed based on the SPIRIT 2013 Statement (Standard Protocol Items: Recommendations for Interventional Trials) (Supplemental Material 1).^
66
^

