#### Guolin Qigong

Participants in the intervention group will attend a 2-hour supervised face-to-face (F2F) GQ training class for 12 weeks with home-practice on non-class days. There will be 2 training classes per week for the first 2 weeks and once per week for the next 10 weeks.

The GQ training involves a modified version of a Chinese medical qigong therapy often referred to as “walking qigong” developed by Guo Lin.^
38
^ GQ was developed specifically for cancer and consisted of several breathing and moving exercises. The GQ training in the current study includes the following 3 main exercises:

1. Feng Hu Xi Zhi Ran Xing Gong (Natural Wind Breathing Walking)

Participants walk in a circle, synchronizing their breathing, arm movements, and steps focusing on the movement of their body with the goal of calming one’s mind, relaxing various parts of the body and the mind, and revitalizing the “life-force,” that is, *qi*.

2. Dian Bu Gong (Step Tap Method)

A modified natural Wind Breathing Walking Exercise with additional step tap.

3. Sheng Jiang Kai He Fa (Ascending, Descending, Opening, and Closing Method)

A calming and relaxation method of synchronized arms and legs movements on the spot which can be practiced within limited space.

Each main exercise has to be practiced separately as individual sets comprising 3 parts:

a. Preparatory relaxation exercise (gentle breathing and meditation; 4 minutes):

In relaxed standing posture, synchronize the breath with gentle arm movements in front of the abdomen (opening and closing of the Dantian). Dantian is a Chinese medicine concept that refers to the “elixir field” or “energy center.” It has different locations but often referred to the lower abdomen between the navel and pubic bone of the human body.^73,74^

b. Main exercisei. Feng Hu Xi Zhi Ran Xing Gong (Natural Wind Breathing Walking) orii. Dian Bu Gong (Step Tap Method) oriii. Sheng Jiang Kai He Fa (Ascending, Descending, Opening, and Closing Method).c. Concluding exercise: breathing exercises, opening, and closing of the Dantian, and self-massage (3-6 minutes).^
50
^

Please refer to Supplemental Material 2 for detailed steps. All movements will include modifications to enhance safety. Participants will be advised to rest as and when necessary, according to their health status.

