### Usual Care Waitlist Control

Participants in the usual care waitlist control group will be advised to continue with their usual care routines and exercises and will be asked not to attend any other Qigong exercises. They will be offered to attend the same GQ training class after Week-16 of the GQ training of their cohort.

However, to maintain integrity of the study, instructors will not be informed about the allocation of participants. Consequently, when instructors commence training of subsequent cohorts, they will be unaware of which participants belong to the intervention group (commencing from Week 1), and which are part of the control group (joining the GQ group in Week 1), given the GQ training will be offered continuously. This ensures the instructors are effectively blinded to the allocation to maintain impartiality in the delivery of the training and minimizes any potential biases that may arise from instructor knowledge of group allocation.

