### Sample Size

Using a small effect size (0.2)^
65
^ rather than a medium effect size (0.5)^
64
^ to achieve a more conservative estimation, the sample size is 25 cases in each group with 90% power and two-sided 5% significance trial design.^
88
^ Allowing for a drop-out of about 20% based on previous studies,^89
[Bibr bibr90-15347354241252698][Bibr bibr91-15347354241252698]-92^ a total sample of 60 (30 in each group) would be required.

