## Data Analysis

### Quantitative Data

Data analysis will be conducted by an independent statistician. Data analysis will be by intention to treat using last observation carried forward (LOCF).^
93
^ The normality of the study data will be checked by examining the mean, median, skewness, and kurtosis including graphical representation of the box plot, normal Q-Q Plot or histogram. Continuous data will be summarized using descriptive statistics including the number of observations used in the calculation (*n*), mean, standard deviation (SD), minimum, median and maximum. Categorical data will be summarized as counts and percentages of each category. Between group comparison will be conducted using the t test, chi-square test, or Fisher exact test, as appropriate. We will report the results for two-sided 5% tests for the primary trial outcome. We will use generalized linear mixed model (GLMM). The outcomes of the model will be BFI, PSQI, CES-D scores, and 24-hour urine cortisol test results. Models will include the treatment group as a fixed effect, with time as a random effect to account for the repeated measurements. Analyses will be conducted to identify the baseline characteristics of the participants who may benefit most from the intervention. Model assumptions will be checked and appropriate adjustments to the analysis will be made where necessary. STATA^®^ software version 17.1 (2021; Stata Corporation, College Station, TX, USA) will be used for all analyses. Cohen’s D will be calculated as the absolute differences between the mean change in the variable divided by pooled variance of the change.

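### Only the Guolin Qigong arm is taught in classes, yet the efficacy analyses have no class term; if outcomes correlate within class, the secondary-outcome standard errors are understated

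*Protocol article*

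**What the plan says.** All references are to the protocol article. Under Randomization and Blinding, allocation is by individual, using minimisation. Under Guolin Qigong, delivery in the active arm is by class: "Participants in the intervention group will attend a 2-hour supervised face-to-face (F2F) GQ training class for 12 weeks", twice weekly for two weeks and weekly for the next ten, which makes 2 × 2 + 10 = 14 sessions, with home practice on other days. Under Usual Care Waitlist Control, controls keep to their usual routines: "They will be offered to attend the same GQ training class after Week-16 of the GQ training of their cohort". The same section refers to later cohorts and to training that runs without a break.

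Under Data Analysis, Quantitative Data, the group comparison uses a t test (or chi-square or Fisher exact test), and the mixed model for BFI, PSQI, CES-D and cortisol is set out as follows: "Models will include the treatment group as a fixed effect, with time as a random effect to account for the repeated measurements". No class or cohort term appears. Under Sample Size, "the sample size is 25 cases in each group with 90% power and two-sided 5% significance trial design", with no design effect.

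**The concern.** Up to Week-16 the GQ arm shares sessions and peers while the control arm does not. The design is therefore partially nested: individually randomised, but clustered by class in one arm only. A t test, or a model without a class term, treats between-class variation in the GQ arm as if it averaged out over independent people. If that variation exists, confidence intervals are too narrow and the two-sided 5% level is exceeded, so an unusually good or bad class can pass as an effect of GQ.

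This is distinct from correlation between visits within a person. A participant random effect deals with the latter and leaves class-level variation untouched.

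**Working it through.** **The plan's own figure.** A two-sample comparison at a standardised effect of 0.2, 90% power and two-sided 5% needs 526 per arm. With 25 per arm the power at 0.2 is about 10.5%, and 90% power is reached only at an effect of about 0.94. The stated 25 per group is thus not reproduced by this calculation. That is a separate matter and is not used below, except that 0.94 serves as a reference effect for power. The step to 30 per arm matches 25 × 1.2 = 30.

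**Inputs from the article.** 30 per arm; 1:1 allocation; two-sided 5%; classes in the GQ arm only until after Week-16.

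**Assumptions, because the article gives no figure.** Class-level ICC of 0.01, 0.05 or 0.10; the 30 GQ participants split equally into 6, 3 or 2 classes, so class size m = 5, 10 or 15.

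**Formulae.**
- Design effect in the GQ arm: DE = 1 + (m − 1) × ICC.
- The analysis that ignores class takes the variance of the difference as σ²(1/30 + 1/30). The actual variance is σ²(DE/30 + 1/30). The ratio of true to naive standard error is therefore √((DE + 1)/2).
- Actual two-sided error: 2 × [1 − Φ(1.96 / ratio)].

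Worked case, m = 10 and ICC 0.05: DE = 1 + 9 × 0.05 = 1.45; ratio = √(2.45/2) = 1.107; error = 2 × [1 − Φ(1.771)] = 7.7%.

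| ICC | Class size (classes) | DE | True/naive SE | Actual error, formula | Actual error, simulated t test |
|---|---|---|---|---|---|
| 0.01 | 5 (6) | 1.04 | 1.010 | 5.2% | 5.4% |
| 0.01 | 10 (3) | 1.09 | 1.022 | 5.5% | 5.5% |
| 0.01 | 15 (2) | 1.14 | 1.034 | 5.8% | 5.8% |
| 0.05 | 5 (6) | 1.20 | 1.049 | 6.2% | 6.3% |
| 0.05 | 10 (3) | 1.45 | 1.107 | 7.7% | 7.7% |
| 0.05 | 15 (2) | 1.70 | 1.162 | 9.2% | 8.9% |
| 0.10 | 5 (6) | 1.40 | 1.095 | 7.4% | 7.1% |
| 0.10 | 10 (3) | 1.90 | 1.204 | 10.4% | 10.2% |
| 0.10 | 15 (2) | 2.40 | 1.304 | 13.3% | 13.8% |

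The simulation used 20,000 trials per row, with independent controls and class random intercepts in the GQ arm. With an ICC of 0 the error stayed at about 5%.

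**Does a class-respecting test repair this?** A test of GQ class means against individual controls, with Satterthwaite degrees of freedom and an ICC of 0.05, gave simulated error of 5.0% with 6 classes, 4.9% with 5, 6.1% with 3 and about 8% with 2. It works from about five classes upward and not with two. At the reference effect of 0.94 with 24 to 25 per arm, its power was 82% with 5 or 6 classes and 68% with 3, against 87% to 89% for the t test that ignores class.

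**The mixed model.** The table describes a t test at one visit. The mixed model as written also names no participant effect. For a group effect over four visits with an assumed within-person correlation ρ of 0.4 to 0.8, ignoring that correlation gives a true/naive ratio of √(1 + 3ρ), that is 1.48 to 1.84. This is larger than any class effect in the table, so a class term alone would not make that model sound.

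**The case against.** The strongest reply is that nothing in the article shows a positive class-level ICC. At 0.01 the inflation is negligible to small. This stands: a reader might infer that the standard errors are certainly too small, and the article does not support that.

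Second, the waitlist section gives controls a cohort too, so cohorts contain both arms. An effect of cohort or calendar time common to both arms cancels from the comparison, and ignoring it makes the naive test slightly conservative. This also stands. Only correlation created by the class within the GQ arm counts. Because training is continuous, closed classes of 5 to 15 are likewise an assumption.

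Third, one might point to instructors as a source of clustering. The article appears to describe the same two instructors throughout, so instructor is not shown to vary by class. Shared sessions and peers remain as possible sources; home practice may dilute them.

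Fourth, the outcomes affected are secondary in a feasibility trial. It would be wrong to infer that the primary feasibility result is compromised. Yet the article hypothesises benefit on these outcomes and justifies its size by power at a 5% level, so their intervals will be read as evidence.

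Finally, a condensed article may leave detail to an analysis plan, and it allows adjustments after model checks. But it does state the model's terms, and they do not match the delivery it describes. The distributional checks it lists would not reveal class correlation.

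**Conclusion.** The point holds conditionally. The stated analyses omit the class structure that exists only in the GQ arm, and any positive within-class correlation there would understate the standard errors of the secondary efficacy outcomes. Over the assumed range the effect runs from negligible (error of about 5% to 6% at ICC 0.01) to material (7% to 13% at ICC 0.10), with 6% to 9% at ICC 0.05. These figures rest on 30 GQ participants in 2 to 6 equal classes and on ICCs that the article does not give. It is worth correcting because the change is cheap, but it is no reason to doubt the trial's primary aim.

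**What to change.** In Data Analysis, Quantitative Data:
- Record the class of each GQ participant, and define beforehand what counts as a class if entry is rolling.
- Base the efficacy comparison on a model with a participant random intercept, which the repeated measures need in any case, and with time and group-by-time as fixed effects.
- With about five or more classes, add a class random effect that applies to the GQ arm only, with small-sample degrees of freedom (Satterthwaite or Kenward-Roger), and report the estimated class ICC with its interval.
- With fewer classes, keep the participant-level model and also report the treatment-effect interval at fixed class ICCs of 0.01, 0.05 and 0.10. In simulation such intervals held about 5% error when the assumed ICC was right.

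In Sample Size, state that the figure assumes independent participants.

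The cost is analysis wording and one extra variable that class records should supply; no extra participants or visits. Intervals become somewhat wider, the class ICC will be imprecise, and with very few classes the loss of power may be material.

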### Randomization and Blinding

After informed consent, participants will be randomly assigned to either the GQ or usual care waitlist control group at a 1:1 ratio with the random sequence generated by an online computerized randomization system using minimization method^70
[Bibr bibr71-15347354241252698]-72^ by an independent research assistant.

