### Study Assessments

The variables under consideration will encompass basic demographic data, primary outcomes, and secondary outcomes. Basic characteristics will be collected at baseline (Week-1).

Primary feasibility outcomes on adherence, attendance, and any adverse events will be recorded throughout the intervention period from Week-1 to Week-12 in the practice diary by the participants. Secondary patient-reported outcomes on fatigue, depression, and sleep will be measured at baseline (Week-1), mid-intervention (Week-6), post-intervention (Week-12), and 4 weeks after completion of intervention (Week-16). Urine samples (for urine cortisol test) to assess 24-hour urinary cortisol will be collected a day prior to enrollment date and post-intervention (Week-12). Primary feasibility outcomes and secondary patient-reported outcomes will be assessed by an independent research assistant to minimize bias. A summary of the planned data collection is shown in Figure 2.

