#### Patient-reported outcomes and cortisol biomarker

i. Patient-reported outcomes

Participants will complete several patient-reported outcome measures to evaluate fatigue—Brief Fatigue Inventory (BFI),^
68
^ sleep quality—Pittsburgh Sleep Quality Index (PSQI)^
76
^ and depression—Centre for Epidemiologic Studies Depression (CES-D)^77,78^ at Week-1, Week-6, Week-12, and Week-16.

a. Fatigue—The Brief Fatigue Inventory (BFI)

The BFI was developed for the rapid assessment of fatigue severity in cancer patients for use in both clinical screening and clinical trials. It is easy to administer, and patients can complete them easily as it has only 9 items with simple wordings that are easy to understand and translate.^
68
^ Items 1 to 3 rate participants’ worst, usual, and current fatigue during the past 24 hours using a visual analog scale (VAS) ranging from 0 (no fatigue) to 10 (very severely fatigued). A composite fatigue severity score was obtained by averaging the 3 severity scores. The remaining 6 items rate the level at which patients` fatigue interferes with certain functions such as daily activity, work, walking ability, normal work, relations with others, and enjoyment in life. Each item is rated on a scale of 0 (does not interfere) to 10 (completely interferes). A composite fatigue interference score will be obtained by averaging the scores of the 6 interference items. Severity scores of 1 to 3 suggest mild fatigue, 4 to 6 moderate, and 7 to 10 represent severe fatigue. The internal consistency Cronbach’s α at .96 supports the reliability of BFI which is correlated with measures of performance status (patients who are more ill reported higher levels of fatigue).^
68
^

b. Sleep—Pittsburgh Sleep Quality Index (PSQI)

The PSQI, proposed by Buysse et al^
76
^ in 1989, is currently the most commonly used scale for assessing sleep quality. The PSQI is a 19-item scale measuring 7 aspects of the sleep quality and disturbances, that is, subjective sleep quality, sleep latency, duration, efficiency, disturbances, use of sleep medication, and daytime sleep dysfunction, each weighted equally on a 0 to 3 scale. The total score ranges between 0 and 21, with increasing scores indicating worse sleep quality.^
76
^ It has a sensitivity of 89.6% and a specificity of 86.5% to detect insomnia cases and is a useful first-line, easy-to-handle, and time-efficient questionnaire to evaluate sleep quality.^
79

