^ The PSQI was reported to be a stable measure of sleep quality with high test-retest reliability and construct validity.^79,80^

c. Depression—Centre for Epidemiologic Studies Depression (CES-D)

The CES-D is a short self-reported 20-item scale^
81
^ to be administered to measure depression symptoms at baseline, mid-intervention, post-intervention, and follow-up. The CES-D shows very high internal consistency and adequate test-retest repeatability.^
81
^ The score is the sum of all items, and the maximum score is 60. Scores ≥ 16 on the CES-D is considered as having “depressed symptoms.” The cut off score of 12 has been validated with DSM-III criteria for clinical depression.^81,82^

ii. Cortisol biomarker: 24-hour urine cortisol

Urine sample will be collected at baseline (Week-1) and post-intervention (Week- 12).^
83
^ Participants are briefed on the urine collection procedure during assessment and advised to obtain the 2.5 L urine collection container from any nearby BP Laboratories before baseline (Week-1) and post-intervention (Week-12). We use 24-hour urinary cortisol as a non-invasive, integrated measure of cortisol stress hormone activity that could be collected in participants’ home environments. Participants are instructed to collect all urine for 24 hours from 8:00am a day prior to baseline (Week-1) and post-intervention (Week-12) to 8:00am the next mornings and to send the urine sample collected to the nearest BP Laboratories the next morning itself. If the 2.5L collection container is completely full, subjects are advised to use a clean mineral water bottle to collect any specimen in excess of the 2.5 L collection. If subjects are unable to collect all urine for any reason, their samples will be deemed inadequate and no urinary cortisol data will be recorded for these subjects.

The 24-hour urine cortisol test provides a more accurate estimate of overall cortisol secretion^
84
^ to assess urinary-free cortisol (UFC) over a 24-hour period and provides an index of (unbound serum cortisol) the total amount of cortisol released by the adrenals. The 24-hour collection time reflects the amount of cortisol that is released over a complete circadian cycle, which is a physiologically meaningful unit of time. An integrated mean of cortisol levels over a 24-hour period is thought to provide a moderately stable measure of adrenocortical output.^
85

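### The efficacy model uses a random effect for time, not participant, to handle repeated measures and has no group-by-time term: standard errors are too small as written, and the group effect is diluted wherever Week-1 is an outcome

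*Protocol article*

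**What the plan says.** The only efficacy model is in the Quantitative Data section of the protocol article. On its outcomes: "The outcomes of the model will be BFI, PSQI, CES-D scores, and 24-hour urine cortisol test results". On its terms: "Models will include the treatment group as a fixed effect, with time as a random effect to account for the repeated measurements". Treatment group is the only fixed effect named. The article mentions no participant-level effect, fixed visit effect, group-by-time term or baseline covariate.

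The section on patient-reported outcomes and the cortisol biomarker sets the visits. The three questionnaires are completed "at Week-1, Week-6, Week-12, and Week-16". Urine is collected twice, at baseline and at Week-12.

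The same analysis section also plans between-group t tests, last observation carried forward, and an effect size built on change: "Cohen’s D will be calculated as the absolute differences between the mean change in the variable divided by pooled variance of the change".

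**The concern.** There are two separate problems.

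- **Correlation.** Repeated measurements need special handling because values from the same person resemble each other. The sentence gives that job to time. A random effect indexed by time adds a shift common to everyone at a visit. Both arms are present at every visit, so the shift cancels from the group comparison, and the within-person correlation stays unmodelled. Four values from one person then count as four independent values.
- **Estimand.** With group as the only fixed effect, its coefficient is an average group difference over all modelled visits. If Week-1 is one of them, the average includes a difference whose expectation is zero under randomisation.

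The study hypothesis includes benefit on fatigue, sleep, depression and cortisol, and this is the only model specified for them. An analyst who follows the sentence could report differences that are too precise and, where Week-1 is modelled, too small.

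**Working it through.** **Inputs from the protocol article.** Four visits for BFI, PSQI and CES-D (m = 4); two for cortisol (m = 2); two-sided 5% level. The article gives no numerical result for this model, so there is no figure to reproduce. The 25 per group from the Sample Size section cancels from steps 1 and 2.

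**Assumed inputs.** The article gives neither a within-person correlation ρ nor an effect pattern. I take a common ρ of 0.3 to 0.7 and state each effect pattern where it is used.

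**Step 1: correlation ignored.** The true variance of the group difference exceeds the model's by the factor 1 + (m − 1)ρ, so the actual type I error is 2·[1 − Φ(1.96 / √(1 + (m − 1)ρ))].

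| Visits | ρ = 0.3 | ρ = 0.5 | ρ = 0.7 |
|---|---|---|---|
| m = 4, variance factor | 1.9 | 2.5 | 3.1 |
| m = 4, type I error | 15.5% | 21.5% | 26.6% |
| m = 2, variance factor | 1.3 | 1.5 | 1.7 |
| m = 2, type I error | 8.6% | 11.0% | 13.3% |

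Simulation of the literal model (25 per arm, four visits, 500 runs per setting) gave 16.6%, 21.4% and 27.2%. Some fits gave convergence or boundary warnings, but the results agree with the formula. Adding a participant random intercept and a fixed time effect brought the error back to about 5% to 6%.

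If only Weeks 6, 12 and 16 were outcome rows, m = 3 and the factor is 1.6 to 2.4. The same formula gives 2·[1 − Φ(1.96/1.265)] ≈ 12% to 2·[1 − Φ(1.96/1.549)] ≈ 21%, so the problem remains.

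**Step 2: baseline averaged in.** With equal visit weights, the coefficient estimates the mean of the visit-specific effects. Let D be the full effect.

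- Questionnaires, effect 0, D, D, D: 3D/4 = 0.75D.
- Questionnaires, effect 0, D/2, D, D: 2.5D/4 = 0.625D.
- Cortisol, effect 0, D: D/2 = 0.50D.

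Simulation of the constant pattern with D = 0.5 gave a mean estimate of 0.386, against 0.75 × 0.5 = 0.375 expected.

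A participant random intercept keeps the weights equal, so the constant pattern stays at 0.75D. A participant intercept plus random slope on time (assumed slope SD 0.02 to 0.05 per week) puts more weight on baseline and gives about 0.54D to 0.71D.

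**Step 3: is Week-1 an outcome row?** For cortisol it must be: there are only two measurements, so nothing is repeated unless baseline is modelled. For the questionnaires it is the natural reading, because one sentence covers all four outcomes. It is not the only reading, since Weeks 6, 12 and 16 are themselves repeated measurements.

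**The case against.** The strongest reply is that the sentence is shorthand. Its stated purpose is to handle repeated measurements, and time as a random effect may mean a participant-level coefficient on time. On that reading the correlation is at least partly modelled and the inflation in step 1 largely goes. This is possible, but the text does not say it. The article names the terms and gives the role to time, so this is a rule stated wrongly and not a detail left to an analysis plan. The dilution in step 2 does not depend on this question. The general promise to check model assumptions supplies no missing term and does not change what the coefficient estimates.

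A second reply is that Week-1 may not be an outcome for the questionnaires. That stands, and it makes their dilution conditional.

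Four stronger inferences are tempting, and the documents do not support them:

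- **Every planned effect estimate is diluted.** Cohen's d is built on change, and its numerator does not average in baseline.
- **A baseline-adjusted Week-12 analysis always gains power.** Take 25 per arm, a constant post-baseline effect of 0.5 SD and ρ = 0.3. The group main effect with a correct standard error has power Φ(0.375/√(0.08 × 1.9/4) − 1.96) = 49%. The adjusted Week-12 contrast has Φ(0.5/√(0.08 × 0.91) − 1.96) = 46%. At ρ = 0.7 the order reverses, 33% against 70%. The documents fix neither the pattern nor ρ.
- **Known minimisation factors have been left out.** The Randomization and Blinding section names the method but no factors.
- **The trial's main conclusion is at risk.** Feasibility is primary, and this model serves secondary outcomes.

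**Conclusion.** The point holds, at moderate severity. Taken as written, the model leaves within-person correlation unmodelled. For assumed ρ of 0.3 to 0.7, type I error is about 16% to 27% with four visits and 9% to 13% with two. This part rests on the literal reading.

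The dilution is firm for cortisol, where the group coefficient estimates half of the Week-12 effect. For the questionnaires it is about 0.63 to 0.75 of the post-baseline effect under the two patterns shown, provided Week-1 is an outcome row. Intending participant random effects would not remove it.

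Carrying the last observation forward copies values within a person and would tend to raise the ignored correlation; this was not quantified.

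**What to change.** Replace the model sentence with the following content:

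- **BFI, PSQI and CES-D:** a linear mixed model with a participant random intercept, or a within-participant covariance structure. Fixed effects are group, visit as a category, and group-by-visit. Baseline score enters as a covariate, with Weeks 6, 12 and 16 as outcomes, or baseline stays in the outcome with the group means constrained to be equal at Week-1.
- **Reporting:** the group difference at each post-baseline visit, with one visit named in advance as principal. Week-12, the end of the intervention, is an obvious candidate, but the article names none and the choice belongs to the investigators.
- **Cortisol:** ANCOVA of the Week-12 value on the baseline value.

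The cost is a few lines of wording and code and a few degrees of freedom. No new data are needed. With about 50 completers, a random intercept is the cheaper covariance choice.

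### Cohen's D is defined with the pooled variance as its denominator; applied as written it gives d divided by the SD of change, which depends on the unit of measurement

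*Protocol article*

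**What the plan says.** The Quantitative Data section of the protocol article ends with a definition: Cohen's D "will be calculated as the absolute differences between the mean change in the variable divided by pooled variance of the change". I found no other definition of the effect size in the article, and nothing that corrects this one.

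The same section lists what is to be modelled: "The outcomes of the model will be BFI, PSQI, CES-D scores, and 24-hour urine cortisol test results". The section on patient-reported outcomes and the cortisol biomarker shows how different the scales are:

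- BFI severity items are rated on a scale "ranging from 0 (no fatigue) to 10 (very severely fatigued", and the composites are averages of items.
- For PSQI, "The total score ranges between 0 and 21, with increasing scores indicating worse sleep quality".
- For CES-D, "The score is the sum of all items, and the maximum score is 60".
- Cortisol is a laboratory measurement, and the article does not state its unit.

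The Sample Size section also works in standardised effects: "Using a small effect size (0.2"), "rather than a medium effect size (0.5").

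**The concern.** The name of the statistic and the formula given for it do not agree. Cohen's d is a pure number because its numerator and denominator carry the same unit. A variance carries the squared unit, so the ratio in the text has the unit of one over the outcome.

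The sentence cannot be put down to condensation for a journal. The article chose to state the formula and stated it wrongly. The same section names the standard deviation correctly for the descriptive summaries, so it uses the right term elsewhere. The analysis is assigned to an independent statistician, who could reasonably code what is written.

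At stake are the published effect sizes for fatigue, sleep, depression and cortisol. A reader would set figures labelled Cohen's D against the usual small and medium values and against each other, and neither comparison would be valid.

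**Working it through.** **Inputs.** From the article: the formula, the four outcomes, and the effect sizes 0.2 and 0.5. Assumed: all SDs of change, because the article gives none. I read the numerator as the difference between groups in mean change; the algebra is the same for any numerator in the outcome's own unit. The article reports no value of Cohen's D, so there is no figure to reproduce.

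**Step 1: algebra.** Let Δ be the absolute difference in mean change and S the pooled SD of change.

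- Cohen's d = Δ / S
- Statistic as written = Δ / S² = (Δ / S) / S = d / S

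The error factor is exactly 1/S. The two agree only at S = 1. Above 1 the written formula understates d; below 1 it overstates d (at S = 0.5, a d of 0.5 becomes 0.5/0.5 = 1.0).

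**Step 2: unit check.** Take Δ = 10 and S = 20 in some unit.

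- d = 10/20 = 0.5; as written, 10/400 = 0.025.
- Express the same data in a unit ten times smaller, so that Δ = 100 and S = 200. Then d = 100/200 = 0.5, unchanged; as written, 100/40,000 = 0.0025.

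The same data give a tenfold different answer after a change of unit.

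**Step 3: size under assumed SDs of change.** Each entry is d/S.

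| Outcome | Assumed S | True d = 0.2 appears as | True d = 0.5 appears as |
|---|---|---|---|
| BFI | 1.5 / 2 / 2.5 | 0.13 / 0.10 / 0.08 | 0.33 / 0.25 / 0.20 |
| PSQI | 2 / 3 / 4 | 0.10 / 0.067 / 0.05 | 0.25 / 0.167 / 0.125 |
| CES-D | 5 / 8 / 10 | 0.04 / 0.025 / 0.02 | 0.10 / 0.0625 / 0.05 |

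For cortisol, any value depends on the unit as well as on the assumed SD. In an arbitrary unit with S = 30, 60 or 100, a true d of 0.5 would appear as 0.017, 0.008 or 0.005.

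**Step 4: what this does to comparisons.** A true 0.5 on BFI with S = 2.5 would print as 0.20, the value that the Sample Size section calls small. The order of outcomes can also reverse. CES-D with d = 0.8 and S = 8 gives 0.8/8 = 0.10, while BFI with d = 0.3 and S = 2 gives 0.3/2 = 0.15, so the weaker effect looks the stronger.

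**Step 5: after correction.** With S in the denominator, 0.2 stays 0.2 and 0.5 stays 0.5 at every SD and in every unit.

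**The case against.** The best defence is that this is a slip of one word. The sentence names a standard statistic, an independent statistician will run it in standard software, and the name may prevail over the gloss. The trial is also a feasibility study: its primary outcomes are recruitment, retention, attendance, home practice, missing data and safety, and this effect size only supplements the analysis of the secondary outcomes. Both points are fair. They limit the consequence but do not make the sentence right, and code that used the SD would depart from the published formula.

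A reader might infer more than the article supports:

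- *That reported effect sizes are already wrong.* This is a plan. The error arises only if the formula is applied literally.
- *That the next trial would be sized wrongly.* The article nowhere says that this d will be used for that purpose. Its Conclusion says only that the findings may inform later design. The Quantitative Data section also plans n, means and SDs for continuous data, which a later planner could use instead.
- *That taking the absolute difference would hide harm.* It removes the sign from this one figure, but the group means and the model's group effect would still show direction. An unsigned d is a presentation choice.
- *That the effect should be standardised by the baseline SD or taken from a baseline-adjusted model.* Standardising change by the SD of change is legitimate. The article does not say how the 0.2 and 0.5 were standardised, so a baseline SD cannot be shown to match them better.
- *That the Sample Size section repeats the error.* It does not use this formula. It matters here only because its 0.2 and 0.5 are on a scale that the written statistic would not share.

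**Conclusion.** The definition is wrong as written. The factor of 1/S and the dependence on unit follow from algebra and need no assumption. The numerical ranges illustrate the size only, because they rest on assumed SDs of change; the trial's own SDs will determine the actual distortion.

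The effect is confined to the effect sizes reported for BFI, PSQI, CES-D and cortisol. The between-group tests and their p-values, the mixed-model estimates, the sample size and the feasibility outcomes make no use of this statistic. That is a statement about what depends on the formula, not a check of those other elements. This is a minor error with a plain correction, to be made before the analysis.

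**What to change.** In the last sentence of the Quantitative Data section, replace variance with standard deviation, so that the denominator is the pooled standard deviation of the change. Check that any analysis code already written uses the same denominator. The cost is one term in the text and at most one line of code, with no effect on data collection or on other analyses.

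Reporting d with its sign and a 95% confidence interval would make it more useful, but this is optional and is not needed to correct the error.
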